## Abstract

**Background::**

Pain management after the total joint arthroplasty is still challenging, but worthy of attention, because good pain management can improve the outcomes of patient. It is still controversial whether fascia iliaca compartment block (FICB) can effectively decrease the opioid consumption and pain after total hip replacement (THR) owing to the number of published investigations is small. The purpose of this present study is to assess the efficacy and safety of FICB for postoperative analgesia after THR.

**Methods::**

This is a single center, placebo-controlled randomized trial which is performed in accordance with the SPIRIT Checklist for randomized studies. It was authorized via the Chifeng Municipal Hospital institutional review committee (H2020-19-8). 100 patients undergoing THR will be included in this study. Patients are randomly divided into 2 groups: FICB group or Non-FICB group, FICB with 5mgmL^–1^ of epinephrine and 40 mL of ropivacaine 0.2%. Primary outcomes are pain score at different time point. Visual analog scale is used to assess the pain (10: the maximum possible pain and 0: absent pain). The secondary outcomes are the postoperative complications, length of hospital stay and total consumption of opioid. All the needed analyses are implemented through utilizing SPSS for Windows Version 15.0.

**Results::**

Figure 1 will show the primary and secondary outcomes.

**Conclusion::**

This trial can provide an evidence for the use of FICB for analgesia after THR.

## Introduction

1

Total hip replacements (THRs) are quite successful surgery for many end-stage hip diseases in terms of pain relief and functional recovery.^[1,2]^ And the demand for primary THR is projected to grow by 3.48 million procedures in the United States alone by 2030.^[3,4]^ However, THR are associated with severe perioperative pain which prolongs length of hospitalization and increases the morbidity and medical cost.^[5,6]^ Adequate pain management is crucial for improving the satisfaction of patients and clinical outcomes. Numerous strategies have been implemented to reduce postoperative pain following THR including local infiltration analgesia, epidural analgesia, intravenous non-steroidal anti-inflammatory agents and peripheral nerve block.^[7–9]^ Each method has its limitations and opioids are used as an alternative method to reduce pain. However, opioid can cause many side effects, such as gastrointestinal reactions, respiratory depression, retention of urine and constipation.^[10,11]^ Therefore, multimodal analgesia has been extensively used in perioperative period of THR.

Fascia iliaca compartment block (FICB) is a kind of anterior method to lumbar plexus. The hip joint is supplied via the branches of sciatic, obturator, and femoral nerves.^[12]^ They are all the part of lumbar plexus, which means that blocking lumbar plexus provides an elegant method for the postoperative analgesia after THR. FICB has no effect on muscle strength of quadriceps femoris and theoretically, it will not increase the risk of fall during rehabilitation. Several articles have suggested that FICB was related to the reduced consumption of opioid analgesics and the improvement of pain relief in patients with THR.^[13,14]^ However, others reported that there was no positive effects for postoperative pain management.

It is not clear that whether FICB is a kind of effective approach for the postoperative analgesia after THR. Therefore, we conduct this randomized controlled study protocol in order to evaluate the efficacy and safety of FICB for analgesia after THR. Our assumption is that FICB could reduce the consumption of opioid and pain score after operation in the early postoperative period.

## Methods

2

This is a single center, placebo-controlled randomized trial which is performed in accordance with the SPIRIT Checklist for randomized studies. It was authorized via institutional review committee in the Chifeng Municipal Hospital (H2020–19-8) and then was registered in research registry (researchregistry5894). The orthopedic surgeon will explain the details of trial, afterward, patiently answer all the questions from patients. These patients are then presented with the written information of our trial. Each of patient received a written informed consent. Since all patients participated voluntarily, they could withdraw at any time during the trial.

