### Subjects

2.1

100 patients undergoing THR will be included in this study. In the random envelope, all participants will be assigned a random number via utilizing the random number table, and the result of allocation is hidden. Patients are randomly divided into 2 groups: FICB group (n = 50) or Non-FICB group (n = 50), FICB with 5mgmL^−1^ of epinephrine and 40 mL of ropivacaine 0.2%. Physicians, statisticians, data collectors and evaluators are all blinded to the allocation.

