### Anesthesia

2.3

Patients are given intravenously 0.02mgkg^−1^ of midazolam and 0.5mgkg-^1^ of fentanyl. All patients will undergo the spinal anesthesia in lateral position. The level and midline of the intervertebral spaces of L3–4 and L4–5 are determined, afterward, spinal anesthesia is performed by injecting 10 mg 0.5% bupivacaine hyperbaric solution with the 25-gauge Quincke needle. Patients are placed promptly in supine position. After the addition of 18 intravenous cannula to the ankle, all the patients receive THR in an independent lateral position via a hip surgeon with fifteen years of experience. The patient is then transferred into a separate ward. After the standard monitoring, the patients in group FICB are performed with ultrasound; Afterward, both 2 groups of patients start the patient-controlled intravenous analgesia.

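### The trial is labelled placebo-controlled, but no placebo or sham block is described for the Non-FICB arm, and patients are not among the roles listed as blinded

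*Protocol article*

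**What the plan says.** The label appears twice in the protocol article, in the abstract and at the start of section 2: "This is a single center, placebo-controlled randomized trial which is performed in accordance with the SPIRIT Checklist for randomized studies".

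Section 2.1 names the arms as FICB and Non-FICB, 50 patients each, and gives an injectate for FICB alone. On concealment it says that "the result of allocation is hidden". On blinding it says: "Physicians, statisticians, data collectors and evaluators are all blinded to the allocation". Patients are not mentioned in that sentence.

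Section 2.3 sets out what happens after surgery and transfer to the ward: "the patients in group FICB are performed with ultrasound; Afterward, both 2 groups of patients start the patient-controlled intravenous analgesia".

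Section 2.4 describes one block technique. The only saline in the article is there, as a step in the active block. Section 2.5 makes VAS pain scores (0 to 10) the primary outcome and total opioid consumption a secondary one.

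**The concern.** A placebo control is a specific design property. It tells the reader that both arms underwent something that looked and felt alike, so that patients' expectations are balanced. The procedures in sections 2.1, 2.3 and 2.4 do not provide this. One arm has a needle procedure under ultrasound and, as far as the text goes, the other has nothing in its place.

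This matters more here than in a trial with a laboratory endpoint. A VAS pain score is ordinarily the patient's own rating, and patients also control their PCA. Both pain and analgesic use can shift if patients know whether they had a block. With no placebo, the comparison estimates the effect of having a block together with any effect of knowing about it. That can be a useful pragmatic question, but it is not the question that a placebo-controlled trial answers.

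**Working it through.** **Step 1: label against procedure.**

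| Item | What the article states | Section |
|---|---|---|
| Design | placebo-controlled | Abstract; 2 |
| Name of the control | Non-FICB, no injectate given | 2.1 |
| Ultrasound procedure | FICB group only | 2.3 |
| Common to both arms after surgery | PCA | 2.3 |
| Saline | one step of the active block | 2.4 |
| Placebo substance or sham for the control | none described | all |

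Section 2.3 assigns steps by arm: "the patients in group FICB are performed with ultrasound", and then "both 2 groups of patients start the patient-controlled intravenous analgesia". The first step is specific to one arm and the second is common. With a placebo injection, the first step would be common too. The label and the procedures therefore cannot both be right as printed.

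**Step 2: who is blinded.**

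- Patients are absent from a list that names four other roles. The statement that the allocation result is hidden follows the description of envelopes and the random number table. It concerns allocation concealment, not what patients know after treatment.
- Physicians are said to be blinded without exception. Whoever performs a block that is given in one arm only knows the allocation. If that person is a physician, the sentence is wrong for that person. It could hold only if the control arm also received an injection from a masked syringe, which the article does not describe.

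**Step 3: illustration of sensitivity.** The article states no SD, effect size or power, so it has no figure to reproduce.

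- From the document: 50 per arm; significance at P < .05 (taken as two-sided).
- Assumed, not in the document: VAS SD of 1.5, 2.0 or 2.5; a shift b in mean VAS due to expectation alone; a true block effect of zero; one time point.

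Standard error: SE = SD × √(2/50) = SD × 0.2, which gives 0.3, 0.4 and 0.5.

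Probability of P < .05 (normal approximation) = Φ(b/SE − 1.96) + Φ(−b/SE − 1.96).

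Example with SD 2.0 and b = 0.5: b/SE = 0.5/0.4 = 1.25, so Φ(−0.71) + Φ(−3.21) ≈ 0.239 + 0.001 = 0.240.

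| Assumed shift | SD 1.5 | SD 2.0 | SD 2.5 |
|---|---|---|---|
| 0 | 5.0% | 5.0% | 5.0% |
| 0.25 | 13.3% | 9.6% | 7.9% |
| 0.5 | 38.5% | 24.0% | 17.0% |
| 1.0 | 91.5% | 70.5% | 51.6% |

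The exact t-test calculation differs only slightly: 37.9%, 23.6% and 16.8% for a shift of 0.5.

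**The case against.** The strongest reply is that this is a condensed article. A placebo injection may be described in the full protocol, and what an article leaves out is not an error. That would answer a complaint about missing detail. It does not answer this one, because the article does say what each arm receives, and that conflicts with its own label. If a placebo exists, sections 2.1, 2.3 and 2.4 misdescribe the control arm. If none exists, the abstract and section 2 carry the wrong label. Published text has to change either way.

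Other parts of the reply stand:

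- A reader might infer that patients are unblinded as a matter of record. The article does not say so. They are only absent from the list, and if they do know their arm, leaving them out is accurate.
- A reader might infer that the plan claims to have excluded expectation bias, or that it calls the trial double-blind. It does neither. Control of that bias is only implied by the placebo label.
- A reader might suppose that evaluators could read the allocation from the groin site. Nothing says that they examine it.
- The term physicians is undefined. It may mean the surgeon, who operates before the block and can be blinded while operating, and ward doctors. Only the block operator is shown to be a problem.
- A no-block comparator is a legitimate design. The fault lies in the description, not in the choice.
- The percentages are ordinary power figures for an assumed shift. A small shift gives small inflation, and no shift gives none.

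**Conclusion.** The point holds as an internal contradiction about a central design feature. The placebo-controlled label disagrees with the procedures described for the two arms, the blinding of patients is not stated although the primary outcome is a VAS pain score, and the blinding of all physicians cannot hold for the operator of a block given in one arm only. As described, the contrast between arms is block effect plus any expectation effect.

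The conclusion rests on the text alone and needs no assumption about size. How large an expectation effect would be, or whether there would be one, cannot be derived from the article. The figure of about 24% (shift 0.5, SD 2.0; 17.0% to 38.5% across SD 2.5 to 1.5) shows only that a modest shift could matter with 50 per arm. It is not an estimate of bias in this trial. It should be corrected before results are reported, because the label decides how readers will interpret them.

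**What to change.** First establish which description is true, then make the abstract and sections 2, 2.1, 2.3 and 2.4 agree.

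**If there is no placebo:**
- Delete placebo-controlled from the abstract and section 2.
- Describe the control as PCA without a block.
- State that patients and the block operator are not blinded, and say which physicians are.
- Keep the block operator out of outcome collection.
- Interpret the result as FICB plus PCA versus PCA alone, without patient blinding.

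**If a placebo or sham was intended:**
- Describe it for the Non-FICB arm.
- State that patients are blinded, and whether the block operator is.
- Confirm that the ethics approval covers it.

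The first route costs a change of wording and one rule on who collects outcomes. Its downside is a weaker but accurate claim about blinding. The second costs a fuller description and a check of the approval, and is open only if the procedure really is part of the trial.

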### Subjects

2.1

100 patients undergoing THR will be included in this study. In the random envelope, all participants will be assigned a random number via utilizing the random number table, and the result of allocation is hidden. Patients are randomly divided into 2 groups: FICB group (n = 50) or Non-FICB group (n = 50), FICB with 5mgmL^−1^ of epinephrine and 40 mL of ropivacaine 0.2%. Physicians, statisticians, data collectors and evaluators are all blinded to the allocation.

### Inclusion and exclusion criteria

2.2

The inclusion criteria included patients aged between 55 and 70 years old, with ASA physical condition I-III, and receiving the total hip arthroplasty in our hospital. The exclusion criteria included refusal or inability to sign the informed consent, intolerance to any drug utilized in our study, BMI above 35 kg/m^2^, with the history of renal and hepatic dysfunction, with the clinical evidence of peripheral neuropathies, coagulation disorders, and opioid dependence.

### Anesthesia

2.3

Patients are given intravenously 0.02mgkg^−1^ of midazolam and 0.5mgkg-^1^ of fentanyl. All patients will undergo the spinal anesthesia in lateral position. The level and midline of the intervertebral spaces of L3–4 and L4–5 are determined, afterward, spinal anesthesia is performed by injecting 10 mg 0.5% bupivacaine hyperbaric solution with the 25-gauge Quincke needle. Patients are placed promptly in supine position. After the addition of 18 intravenous cannula to the ankle, all the patients receive THR in an independent lateral position via a hip surgeon with fifteen years of experience. The patient is then transferred into a separate ward. After the standard monitoring, the patients in group FICB are performed with ultrasound; Afterward, both 2 groups of patients start the patient-controlled intravenous analgesia.

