### Block techniques

2.4

In supine position, the chlorhexidine and betadine are utilized to disinfect inguinal crease area. A 5 MHz-12 MHz linear probe is placed parallel to inguinal ligament at inguinal crease, and the fascia iliaca, fascia lata, femoral artery, femoral nerve as well as iliacus muscle are found. After the probe is rotated 90 to 135 degrees counterclockwise, we makes this probe parallel to vertebral axis. From this view, a 22G Tuohy needle, connected to a venous extension tube between syringe and the needle, is inserted in the plane and then pushed toward the iliacusmuscle and fascia iliaca. After we confirm that the needle passed through the fascia iliaca, we inject the local anesthetic prepared in advance. After the injection of normal saline, we utilize the hydrodissection technique under the guidance of real-time ultrasound. In hydrodissection technique, a small amount of the local anesthetic (1–2 mL) is injected, and then the needle is extended to proximal side for proximal local anesthetic diffusion. Through this hydrodissection process, the needle passes through the proximal end, goes deep into the fascia iliaca, and enters iliac fossa, and only enters space created via the fluid collection. Prior to the entire needle is inserted into skin, this hydrodissection technique need to repeat. And the total volume is 5mgmL^−1^ 0.2% epinephrine and 40 mL of ropivacaine.

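### Section 2.3 prints the intravenous fentanyl dose as 0.5 mg/kg, very probably a unit error and 1000-fold too high if micrograms were meant

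*Protocol article*

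**What the plan says.** Section 2.3 (Anesthesia) of the protocol article opens with the drugs given around the spinal: "Patients are given intravenously 0.02mgkg^−1^ of midazolam and 0.5mgkg-^1^ of fentanyl". No arm is named. The next sentence reads "All patients will undergo the spinal anesthesia in lateral position", so the fentanyl line is naturally read as applying to both arms, which section 2.1 (Subjects) gives as "FICB group (n = 50) or Non-FICB group (n = 50)". The order of the sentences places fentanyl before the spinal, although the text does not state this outright. The spinal drug is also given in milligrams: "injecting 10 mg 0.5% bupivacaine hyperbaric solution".

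No other section gives a fentanyl dose, a total amount or a microgram unit.

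The block solution is described in section 2.1 as "FICB with 5mgmL^−1^ of epinephrine and 40 mL of ropivacaine 0.2%", and the Methods paragraph of the abstract prints the same strength. Section 2.4 (Block techniques) words it differently: "And the total volume is 5mgmL^−1^ 0.2% epinephrine and 40 mL of ropivacaine".

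**The concern.** Fentanyl is dosed in micrograms. An intravenous dose of half a milligram per kilogram is far outside anything that could be sedation for patients under spinal anaesthesia. Section 2.3 describes no airway control or ventilation, so a deliberate very-high-dose opioid technique is not what is being described. The Introduction itself names respiratory depression as a harm of opioids.

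What is at stake is patient safety. This is a treatment dose in the Methods of a trial planned for 100 patients aged 55 to 70 and up to ASA class III, and other groups may copy the line. The comparison between arms is not at stake, because both arms would get the same weight-based dose.

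**Working it through.** **Inputs**

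- Fentanyl 0.5 mg/kg and midazolam 0.02 mg/kg: section 2.3.
- Bupivacaine 10 mg of a 0.5% solution: section 2.3.
- Epinephrine 5 mg/mL, and ropivacaine 0.2% in 40 mL: section 2.1.
- Body weight: not given. The only related limit, in section 2.2, is exclusion for "BMI above 35 kg/m^2", which does not fix a weight. I assume 50, 70 and 100 kg.

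The plan states no total fentanyl dose, so there is no figure of its own to reproduce.

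**Fentanyl.** Total dose = dose per kg × weight.

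| Assumed weight | As printed (0.5 mg/kg) | If 0.5 microgram/kg was meant | Midazolam (0.02 mg/kg) |
|---|---|---|---|
| 50 kg | 25 mg | 25 micrograms | 1 mg |
| 70 kg | 35 mg | 35 micrograms | 1.4 mg |
| 100 kg | 50 mg | 50 micrograms | 2 mg |

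The ratio of the two fentanyl readings is 1 mg / 1 microgram = 1000, whatever the weight. As printed, the fentanyl mass is 0.5 / 0.02 = 25 times the midazolam mass.

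**Are milligrams used sensibly elsewhere in section 2.3?** For the spinal drug, 0.5% = 5 mg/mL, so 10 mg / 5 mg/mL = 2 mL, which is coherent. Midazolam comes to 1 to 2 mg. The doubt in this section is therefore confined to the fentanyl entry.

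**Epinephrine.** If 5 mg/mL applies to the whole 40 mL, the amount is 5 × 40 = 200 mg. In micrograms it would be 5 × 40 = 200 micrograms = 0.2 mg, again a factor of 1000. The ropivacaine is 0.2% = 2 mg/mL, and 2 × 40 = 80 mg. As printed, the additive would outweigh the local anaesthetic by 200 / 80 = 2.5 times.

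Section 2.4 attaches 0.2% to epinephrine. That would be 2 mg/mL, which does not agree with the 5 mg/mL beside it, and section 2.1 gives the percentage to ropivacaine.

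**The case against.** The strongest objection is that the fault may come from reading or typesetting the PDF. A micro sign turned into the letter m would leave a perfectly legible mg, so legibility does not settle the matter. No micro sign or Greek letter appears anywhere in the text, so nothing shows that one would have survived. The fentanyl unit is also visibly disturbed: its minus sign sits outside the superscript, unlike the midazolam unit in the same sentence. A systematic substitution would spoil exactly the two entries that look wrong, fentanyl and epinephrine, and leave midazolam and bupivacaine intact. This stands as a real uncertainty about where the error arose. It does not remove the need for a check, and it does not explain the misplaced 0.2% in section 2.4, which a changed micro sign could not produce.

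Second, the article gives no reference dose, so nothing in it contradicts 0.5 mg/kg, and the factor of 1000 depends on the intended unit being micrograms. That is correct. The judgement rests on basic pharmacology and on the absence of any airway management in the description, and the factor is conditional.

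Third, epinephrine is a separate matter. The 0.2% in section 2.4 is most simply a transposition from ropivacaine, and the 200 mg figure assumes that 5 mg/mL applies to all 40 mL. Both points are fair. The epinephrine entry shows that drug strengths in the article need checking, but the fentanyl finding does not depend on it.

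Finally, prescribing checks would probably stop such a dose, and the full protocol and order sheets are not shown. That lowers the chance of harm, but it is no reason to leave the line as it is.

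**Conclusion.** The concern holds. Section 2.3 prints a fentanyl dose that amounts to 25 to 50 mg at an assumed 50 to 100 kg, and nothing else in the article corrects it. The unit is very probably wrong, by a factor of 1000 if micrograms were meant; that factor does not depend on the assumed weights. Confidence is medium, because a misread micro sign cannot be fully excluded.

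It must be fixed because it is a stated treatment dose for every patient. It changes no sample size, power or error rate and creates no bias between the arms. The document does not show that dosing has begun or that any patient received this amount.

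**What to change.** 1. Check the fentanyl figure and unit in section 2.3 against the published article, the ethics-approved protocol and the anaesthesia order sheet. If the published page shows micrograms, the fault lies in the text copy and no erratum is needed for this line.
2. If milligrams are confirmed in print, correct the line before it is used for dosing.
3. In the same check, confirm the epinephrine strength in the abstract and in sections 2.1 and 2.4, and return the 0.2% in section 2.4 to the drug it belongs to.

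I propose no dose here; the sponsor must confirm the intended one. The cost is one source check and a short erratum, with no change to sample size, outcomes or analysis.

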### Block techniques

2.4

In supine position, the chlorhexidine and betadine are utilized to disinfect inguinal crease area. A 5 MHz-12 MHz linear probe is placed parallel to inguinal ligament at inguinal crease, and the fascia iliaca, fascia lata, femoral artery, femoral nerve as well as iliacus muscle are found. After the probe is rotated 90 to 135 degrees counterclockwise, we makes this probe parallel to vertebral axis. From this view, a 22G Tuohy needle, connected to a venous extension tube between syringe and the needle, is inserted in the plane and then pushed toward the iliacusmuscle and fascia iliaca. After we confirm that the needle passed through the fascia iliaca, we inject the local anesthetic prepared in advance. After the injection of normal saline, we utilize the hydrodissection technique under the guidance of real-time ultrasound. In hydrodissection technique, a small amount of the local anesthetic (1–2 mL) is injected, and then the needle is extended to proximal side for proximal local anesthetic diffusion. Through this hydrodissection process, the needle passes through the proximal end, goes deep into the fascia iliaca, and enters iliac fossa, and only enters space created via the fluid collection. Prior to the entire needle is inserted into skin, this hydrodissection technique need to repeat. And the total volume is 5mgmL^−1^ 0.2% epinephrine and 40 mL of ropivacaine.

